**Fig. 1 Fig1:**
[figure not shown]
Study design

Legend: *VR* virtual reality, *NEPSY-II* Developmental NEuroPSYchological Assessment, 2nd edition, *WISC-IV* Wechsler Intelligence Scale for Children, 4th edition, *CBCL* Child Behavior Check List, *TACQOL* (TA) Children’s Quality Of Life questionnaire

### Intervention and study setting

The rehabilitation trainings are administered in the GRAIL laboratory at the Scientific Institute (IRCCS) E. Medea (Bosisio Parini, Italy). The GRAIL system is an integrated platform equipped with a treadmill on a motion frame, a Vicon motion-capture system (Oxford Metrics, Oxford, UK) and a 180° cylindrical projection screen. The D-flow software controls the relationship between the patient, the scenery and the interactive feedbacks and stimulations. This software runs on Microsoft Windows and it was used to develop the interactive VR applications with a block diagram approach. For the creation of the GRAIL scenes, objects and scenario were modelled separately by means of Google SketchUp while the avatars were created by using MakeHuman and then modified in Blender. The modelling process was first dedicated to the creation of three-dimensional geometries and then to the application of selected materials and textures. Files generated in SketchUp and Blender were exported in the COLLADA interchange format and then imported into Autodesk 3ds Max software. The latter allowed us to convert models in Wavefront OBJ format and to assemble all the models created within the scenery. The whole scene was exported in Ogre format to be used within the D-flow software: the final scene contained the environment and the individual objects.

Two different scenes were developed specifically for this study: the sweet stands’ environment for the pre- and post-training evaluations and the playground scenario for the social prediction training. Both scenes are designed with a linear, 9-m-long path that branches into three 3-m-long streets. At the end of each branch, one of three objects is located in a semicircle at the same distance from the starting point: the playground setting includes a swing, a circular carousel and a rocking carousel, while the sweet stands’ setting includes an ice cream, a donut and a lollipop stand. Furthermore, four different avatars, two male and two female, were designed: they are adolescents, clearly identifiable by body and clothing features (i.e. hair and t-shirt colours). An example of the two scenarios and of the avatars, respectively, for the evaluation and for the training sessions, is reported in Fig. 2.

**Fig. 2 Fig2:**
[figure not shown]
**a** The virtual reality (VR) environment designed for the evaluation sessions. **b** The GRAIL platform and the VR application running a training session; one of the avatars is visible to the subject. **c** The four avatars used during the training session

Before the beginning of the session, the patient wears two reflective markers on the posterior superior iliac spines, that allow the tracing of the patient’s movements and control the virtual environment: to go faster, the patient has to move forward, to slow down they have to move backward, while to turn right or left they have to shift the pelvis right or left. Then, the patient comes up the GRAIL system, the trainer calibrates their starting position and the session can start. Before starting the first evaluation session, a short and effective navigational training is administered to participants with the aim of learning to navigate within the GRAIL VR environments. A physical therapist specifically patented for using GRAIL technology administers all the applications.

### Evaluation sessions

Pre- and post-training evaluation sessions in the sweet stand ’scenario are administered to both the experimental and the control groups. The paradigm exploits a probabilistic design that has already shown its reliability in assessing social prediction abilities, since children with ASD, who show clinically relevant social deficits, were impaired in using contextual priors to predict the unfolding intention of observed actions ahead of realisation [45]. Within a session, events take place in a pseudorandom way in respect to the pre-established probabilities. Specifically, in each trial, one of four avatar moves from the starting point to one of the stands with pre-established probabilities as shown in Table 2:

**Table 2 Tab2:** Example of event probability in a evaluation session with the “sweet stands” scenario

Session A	Stand		
Avatar	Ice cream	Donut	Lollipop
Avatar A	80%	10%	10%
Avatar B	10%	80%	10%
Avatar C	10%	10%	80%
Avatar D	33%	33%	33%

Two different evaluation sessions were generated, changing the avatar-object associations and event sequence, and are presented, respectively, at T0 and T2 in random order. In this way, we avoid repetition of the same events in the two evaluation sessions in order to minimise learning effects. The order of the two sessions is counterbalanced between patients of the same group (e.g. for patient 1 session A at T0 and session B at T2, for patient 2 session B at T0 and session A at T2, etc.). Considering 20 trials per avatar, 80 trials are administered in each session.

The GRAIL therapist asks the patient to move toward the sweet stand chosen by the avatar and activate it before them. In each trial the patient has to reach one of the stands in maximum 15 s and their maximum speed is 2 m/s. The avatar, one per trial and visibly positioned next to the patient, moves towards a stand, reaching it in 10 s. When the participant reaches a sweet stand, the stand is activated providing a visual reinforcement, otherwise the event is interrupted 5 s after the avatar has reached the object and the patients are invited to try again. Furthermore, when the participant anticipates the avatar in reaching the correct stand they also receive an auditory reinforcement (clapping sound), which signals the scoring of a point in the game in addition to visual reinforcement (activation of the object). The object reached by the avatar is always visible to the participant, for both successful and unsuccessful trials, in order to provide information on the avatar’s preferences that can be used in the next trial. Specific features of the application force the patients to move according to the anticipation of the avatars’ preference rather than following their movements. Indeed, the path is a 9-m straight-line trajectory and, then, it splits into three ways. Therefore, participants are not exposed to motion cues concerning avatars’ directions until the crossroad. Moreover, after this division the speed of the avatars equals the maximum available for the patients, so that they cannot be surpassed anymore. This way, patients are prompted to implicitly learn the probabilistic associations between the avatar and the most chosen sweet stand, thus allowing this paradigm to evaluate and improve the ability to form predictive models of others’ behaviour.

For each trial, the D-flow software automatically saves one raw with the following measures in a .txt file:
Duration of the trialMean speed of the subjectSpeed of the subject at specific points of the path (e.g. at 0.5, 1, and 9 m from the starting point)Specific avatarObject selected by the avatarObject selected by the subjectVictory/no victoryIncremental score

At the end of the 80 trials, the D-flow automatically saves the total score of the session in a different .txt file.

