### Outcome measures

Primary outcome measure:
Social prediction ability: performance during the pre- (T0) and post-training (T2) evaluation in the sweet stands’ scenario; standardised beta-coefficients of the regression between accuracy and probability in the testing phase of the validated PC-based Action Prediction task administered before/after the intervention (T0, T2) and at the follow-up visit (T3)

Secondary outcome measures:
Social cognition: Theory of Mind Parts A and B and Emotion Recognition of the NEPSY-II testing batteryImplicit learning: accuracy and reaction time in the familiarisation phase of an Action Prediction taskExecutive functions (inhibition and flexibility): Inhibition test of NEPSY-IIVisual attention: Visual Attention test of NEPSY-IIVisuospatial and visual-perceptual abilities: Geometric Puzzle and Picture Puzzle tests of NEPSY-IIMemory: Memory for Drawings test of NEPSY-IISensorimotor functions: Finger-tapping of NEPSY-IIBehavioural problems: CBCL 6–18, Parent versionOverall functioning and quality of life assessed using the TACQOL questionnaire, presented in two forms: the self-compiled one and the parent-compiled one

To assess training feasibility:
Number of dropouts: number of children who renounce to complete the 2-week trainingNumber of sessions completed per child: total number of sessions performed in front of the total number proposed of eight sessions

To assess training acceptability:
Acceptability questionnaire: an ad-hoc questionnaire completed by participants and another one by their parents after training conclusion (T2) to assess subjective evaluation of training accessibility and efficacy. It is to note that the same questionnaires are fulfilled by the patients of the active control group and their parents

A psychologist, who is not blinded to the intervention assignment, administers all the neuropsychological tests and questionnaires and records the performance during the GRAIL sessions.

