### Statistical methods

Demographic, clinical and neuropsychological variables of the two groups of patients are inspected through descriptive statistics. A *t* test and *χ*^2^ are used to assess the differences between the experimental and control training groups at baseline for continuous and categorical variables, respectively, thus allowing us to verify successful randomisation. For each outcome measure, we calculate the change between T0 and T2 (training effect delta) and between T0 and T3 (follow-up effect). Delta is calculated as the arithmetic difference between the second/third time points and the first time point. The delta values of the two groups for the primary outcome measure are compared using independent sample *t* tests (two-tailed). For the primary outcome measure, a Bonferroni correction procedure will be used to control for multiple comparisons. Multivariate analysis of variance will be used to explore differential effects of the trainings in the secondary outcome measures. As to what concerns missing data, a modified intention-to-treat analysis approach will be adopted, including in the analyses all the participants who had completed the pre- and post-treatment evaluation sessions, even if they had not completed all the training sessions. No imputation of missing data, however, will be used considering the limited sample size and observation points [58, 59]. The stratification factors (i.e. age and FSIQ), will not be considered in the statistical analyses, assuming that the stratification procedure has ensured a balanced distribution across the two groups.

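### The order of the two VR evaluation sessions is counterbalanced but left out of the primary t test, which costs the VR outcome some precision if the sessions differ in difficulty

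*Protocol article*

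**What the plan says.** The Outcome measures section places two measures under the primary outcome. One is "performance during the pre- (T0) and post-training (T2) evaluation in the sweet" stands scenario; the other is the standardised beta-coefficient from the PC-based Action Prediction task.

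On the VR measure, the Evaluation sessions section says: "Two different evaluation sessions were generated, changing the avatar-object associations and event sequence". Each patient sees one version at T0 and the other at T2, and "The order of the two sessions is counterbalanced between patients of the same group". Some patients in each arm therefore go A then B, and the others B then A.

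Statistical methods fixes the analysis. The change score is defined there: "Delta is calculated as the arithmetic difference between the second/third time points and the first time point". The comparison is also named: "The delta values of the two groups for the primary outcome measure are compared using independent sample" t tests, two-tailed. No term for session order appears. The age and FSIQ strata are excluded too; they "will not be considered in the statistical analyses, assuming that the stratification procedure has ensured a balanced distribution across the two groups".

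The article does not report that sessions A and B were shown to be equally difficult, and it gives no figure for a difference.

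**The concern.** Counterbalancing makes session order a known design factor. If B is easier than A by f, the change score of every A-then-B patient moves up by f and that of every B-then-A patient moves down by f. With order balanced within arms, this nearly cancels from the difference between arms. It does not cancel from the spread within each arm, and that spread is what the two-sample t test uses for its standard error. The test then carries variance that the design has already balanced.

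At stake are the width of the confidence interval and the power for the VR part of the primary outcome. There is a smaller second effect: where the order split is not the same in the two arms, part of f also enters the estimated group difference.

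**Working it through.** **The plan's own figure.** Estimation of sample size gives 21 per group for d = 0.8, power 0.80, alpha 0.05, two-tailed. Exact noncentral-t power at 21 per group is 0.716 with these inputs; 26 per group are needed to reach 0.80. The figure of 21 is reproduced with a one-tailed alpha of 0.05. This is a separate matter, but it sets the baseline here: about 0.72 before any loss from session order.

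**Inputs.**
- 21 per group (Estimation of sample size).
- d = 0.8 (same section). It was set on the Action Prediction coefficient, so using it for the VR score is an assumption.
- Two-sided alpha 0.05 (same section). Statistical methods adds: "For the primary outcome measure, a Bonferroni correction procedure will be used to control for multiple comparisons". The number of tests is not stated, so 0.05 is kept below.
- f, the A–B difficulty difference in units of s, the SD of the change within an order group. It is not in the documents; 0.1 to 0.75 is an assumed range.
- Order split. With 21 per arm the closest possible split is 11/10. Which order has the extra patient in each arm is not stated.

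**Formula.** With order coded +1 or −1, change = group effect + f × order + error, with error SD 1 in units of s. The within-arm variance seen by the t test is about 1 + f², so the standard error grows by about √(1 + f²):
- f = 0.1: √1.01 = 1.005
- f = 0.25: √1.0625 = 1.031
- f = 0.5: √1.25 = 1.118
- f = 0.75: √1.5625 = 1.25

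An order term removes f² and lowers the residual degrees of freedom from 40 to 39. At f = 0 that changes power from 0.716 to 0.715. The confidence interval breaks even at f of about 0.04.

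**Simulation, same split (11/10) in both arms.** Values are rounded from simulations of at least 20,000 trials per setting; repeat runs differ by about 0.01.

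| f | Power, t test | Power, order term | Type I error, t test | 95% CI widening |
|---|---|---|---|---|
| 0.1 | 0.71 | 0.71 | 0.05 | 0.5% |
| 0.25 | 0.69 | 0.71 | 0.04 | 3% |
| 0.5 | 0.63 | 0.72 | 0.03 | 12% |
| 0.75 | 0.52 | 0.72 | 0.01 | 25% |

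The model with order keeps a type I error of about 0.05 throughout. In these runs the unadjusted estimate stays at 0.80, so there is no bias.

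**Simulation, opposite splits (11/10 in one arm, 10/11 in the other).** Mean order is +1/21 in one arm and −1/21 in the other, so the unadjusted estimate shifts by 2f/21, about 0.095f. At f = 0.5 that is about 0.05 SD. The direction depends on which arm has the extra patient with the easier session at T2. Unadjusted power, from the split that works against the experimental arm to the split that favours it:
- f = 0.25: 0.67 to 0.72
- f = 0.5: 0.57 to 0.68
- f = 0.75: 0.43 to 0.61

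The order-adjusted model stays at about 0.71 to 0.72 in all of these.

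**The case against.** **The planned test is valid.** Ignoring a balanced nuisance factor is a legitimate, conservative choice, and type I error does not exceed 0.05 in any setting above. This stands in full: the order term is a matter of efficiency.

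**f may be small.** As described, the sessions differ only in avatar–object mapping and event sequence. The example in Table 2 is symmetric, with three avatars at 80/10/10 and one at equal thirds. The three stands are equally far from the start, and each session has 80 trials, 20 per avatar. This largely stands. The score does depend on learning preferences during the session, so the placing of off-preference trials could matter, and no equivalence check is reported. Even so, nothing in the article points to 0.5 or 0.75.

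**The scope is narrow.** Only the VR measure uses sessions A and B. The Action Prediction coefficient, on which the sample size rests, does not. This stands.

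**Two stronger readings do not hold.** A reader might infer that counterbalancing is wasted unless order is modelled. The article gives the aim of the two sessions as avoiding repeated events and limiting learning effects; it promises no gain in precision. Counterbalancing also keeps session difficulty from being confounded with time, adjusted or not. A reader might also take the lowest power figures (0.67, 0.57, 0.43) as the expected loss. They arise only when the 11/10 splits run in opposite directions against the experimental arm. In the favourable direction there is no loss at f = 0.25.

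**Conclusion.** The point holds as a minor one. The article balances session order by design and then specifies a test for the VR change that ignores it. Any difficulty difference between the sessions therefore inflates the error variance by about 1 + f², which makes the test conservative.

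The size cannot be fixed from the documents. At f = 0.25 or less, with the same order split in both arms, the interval widens by at most about 3% and power falls by about 0.02. At the hypothetical f = 0.5 the power loss is about 0.09. These figures rest on d = 0.8 carrying over to the VR score, alpha 0.05 before any Bonferroni division, and 21 analysed patients per arm.

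A reader might infer that the group comparison is biased. With equal splits it is not. With the closest unequal splits the shift is 2f/21 and can run either way. Missing T2 evaluations could enlarge it, but the documents give no basis for saying by how much.

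**What to change.** In Statistical methods, for the VR evaluation outcome only, replace the two-sample t test on the T2 − T0 change with a linear model of that change on group and session order (A-then-B or B-then-A). Report the group coefficient with its confidence interval. Leave the analysis of the Action Prediction coefficient as it is on this point.

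The cost is one sentence in the plan and one degree of freedom. No new data are needed, because the trial itself assigns each patient's order. The term should be specified before outcomes are compared by group. The Discussion foresees submitting preliminary efficacy data once at least half the target sample has been recruited, and an adjustment added after that would carry less weight.

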### VR-Spirit training

Training sessions adopt the same logic as the evaluation sessions but in the playground scenario. With the aim to balance the association between avatars and objects, four diverse sessions (A, B, C, D) were obtained, such that avatars’ probability of moving toward a specific object is equally distributed across the four sessions. The four sessions are randomly administered during the first week and repeated in the same order in the second week.

Every day, the experimental group is administered with one of the four diverse sessions of the VR-Spirit training so that avatars’ preferences change day by day both in the first and in the second week. Moreover, after the participants have completed the 80 social prediction trials, they also play one of four selected games from the GRAIL kit (see below for the description of the games).

### Active control training

The control group is exposed for the same amount of time (1-h session per day, four sessions per week for 2 weeks) to sessions requiring the participants to play a navigational game, in which they have to conduct a ball out of three mazes, and all four selected GRAIL games. The four selected games are ‘skiing’, ‘balloon shooting’, ‘world soccer’ and ‘traffic jam’. These games have been chosen because they do not present social agents and do not require any form of prediction ability. In the skiing game, participants have to do a slalom between snowmen, scoring a point when they pass each snowman on the right side. In the balloon shooting game, participants have to hit balloons appearing in a natural environment simply by pointing at them. In the world soccer game, children kick a virtual ball toward a goal: they score points when they hit targets put inside the goal. In the traffic jam game, participants are in the middle of a crossroad and they have to raise their left or right foot according to the cars’ movements.

### Outcome measures

Primary outcome measure:
Social prediction ability: performance during the pre- (T0) and post-training (T2) evaluation in the sweet stands’ scenario; standardised beta-coefficients of the regression between accuracy and probability in the testing phase of the validated PC-based Action Prediction task administered before/after the intervention (T0, T2) and at the follow-up visit (T3)

Secondary outcome measures:
Social cognition: Theory of Mind Parts A and B and Emotion Recognition of the NEPSY-II testing batteryImplicit learning: accuracy and reaction time in the familiarisation phase of an Action Prediction taskExecutive functions (inhibition and flexibility): Inhibition test of NEPSY-IIVisual attention: Visual Attention test of NEPSY-IIVisuospatial and visual-perceptual abilities: Geometric Puzzle and Picture Puzzle tests of NEPSY-IIMemory: Memory for Drawings test of NEPSY-IISensorimotor functions: Finger-tapping of NEPSY-IIBehavioural problems: CBCL 6–18, Parent versionOverall functioning and quality of life assessed using the TACQOL questionnaire, presented in two forms: the self-compiled one and the parent-compiled one

To assess training feasibility:
Number of dropouts: number of children who renounce to complete the 2-week trainingNumber of sessions completed per child: total number of sessions performed in front of the total number proposed of eight sessions

To assess training acceptability:
Acceptability questionnaire: an ad-hoc questionnaire completed by participants and another one by their parents after training conclusion (T2) to assess subjective evaluation of training accessibility and efficacy. It is to note that the same questionnaires are fulfilled by the patients of the active control group and their parents

A psychologist, who is not blinded to the intervention assignment, administers all the neuropsychological tests and questionnaires and records the performance during the GRAIL sessions.

### Action Prediction task

We adopt a validated, computer-based Action Prediction task as an experimental outcome measure for social prediction and implicit-learning abilities. This experimental paradigm consists of a probabilistic learning task (familiarisation phase) followed by an Action Prediction task (testing phase). During familiarisation, participants are exposed to videos showing a child actor performing two different grasping actions associated with specific contextual cues and they are asked to recognise the actor’s intention. Notably, in this phase the association between contextual cues and actions was implicitly biased with pre-established probability of co-occurrence. During testing, the second half of the same videos is occluded and the patients are asked to predict the final outcome of the action. Since movement kinematics are ambiguous, responses should be biased toward the contextual priors acquired during the familiarisation phase. For each participant and separately for the two phases, a standardised beta-coefficient is calculated across the trials at the individual level using a regression analysis with probability and accuracy as the independent and dependent variables, respectively. Indeed, the beta-coefficient could be considered as a direct index of the strength of the contextual models of others’ intentions, thus providing a measure of social prediction ability.

